## Abstract

**Background:**

Urinary tract infections (UTIs) are a common cause of prescribing antibiotics in family medicine. In Germany, about 40% of UTI-related prescriptions are second-line antibiotics, which contributes to emerging resistance rates. To achieve a change in the prescribing behaviour among family physicians (FPs), this trial aims to implement the guideline recommendations in German family medicine.

**Methods/design:**

In a randomized controlled trial, a multimodal intervention will be developed and tested in family practices in four regions across Germany. The intervention will consist of three elements: information on guideline recommendations, information on regional resistance and feedback of prescribing behaviour for FPs on a quarterly basis. The effect of the intervention will be compared to usual practice. The primary endpoint is the absolute difference in the mean of prescribing rates of second-line antibiotics among the intervention and the control group after 12 months. To detect a 10% absolute difference in the prescribing rate after one year, with a significance level of 5% and a power of 86%, a sample size of 57 practices per group will be needed. Assuming a dropout rate of 10%, an overall number of 128 practices will be required. The accompanying process evaluation will provide information on feasibility and acceptance of the intervention.

**Discussion:**

If proven effective and feasible, the components of the intervention can improve adherence to antibiotic prescribing guidelines and contribute to antimicrobial stewardship in ambulatory care.

*Trial registration* DRKS, DRKS00020389, Registered 30 January 2020, https://www.drks.de/drks_web/navigate.do?navigationId=trial.HTML&TRIAL_ID=DRKS00020389.

## Background

Urinary tract infections (UTIs) are a frequent cause for patient visits in family medicine, with a prevalence ranging between 1.7 and 3.1% [1, 2]. Affected patients are usually treated with antibiotics as recommended by European guidelines [3]. Based on previous evidence, some guidelines recommend symptomatic treatment and delayed prescription of antibiotics for women with mild to moderate UTI symptoms who would prefer to avoid antibiotics. [4–7]. In the case of antibiotic treatment, guidelines recommend antibiotics with a narrow antimicrobial spectrum (first-line antibiotics), taking into account the local resistance situation [3]. Despite divergent recommendations, second-line antibiotics such as fluoroquinolones, still represent a large proportion of prescribed antibiotics for women with UTIs in Germany [2] and non-antibiotic treatments are rarely recommended [8]. Moreover, data on local resistance patterns of urine bacteria are not yet available for primary care physicians. The resulting inappropriate antibiotic use contributes to increasing resistance rates and weakens antibiotics as an important tool for serious or complicated infections [9, 10].

Implementation of clinical guidelines requires different strategies [11]. Several approaches to improve antibiotic prescribing by healthcare providers in primary care were explored, but none of them could be identified as the most appropriate strategy [12]. A recent Cochrane review investigating whether targeted clinician interventions influence antibiotic prescribing in acute respiratory tract infections found that various interventions such as shared decision-making, educational materials, educational meetings, audit and feedback, the use of point-of-care tests, etc. have impact on prescribing behaviour [13]. Multimodal interventions, such as educational programs with feedback about one’s own prescribing behaviour and the local resistance situation, have also shown positive effects on prescribing quality in ambulatory care [14, 15]. Components of multimodal interventions such as training of physicians in guideline-adherent treatments, audit and feedback to physicians [16], quality circles and prescribing feedback [17] for UTI, an electronic decision support system for medical practice [18] and regionally and nationwide benchmarking with other participating practices (social norm feedback) [19] for infectious diseases in general could improve prescribing quality in primary care. In addition, one study demonstrated a decrease in antimicrobial resistance of uropathogenic bacteria, when FPs followed the guidelines [20].

REDARES aims to implement the recommendations of guidelines in the management of UTIs in primary care, using practice-orientated information. It focuses specifically on the guideline-based selection, and not reduction, of those antibiotics—often required for UTI treatment—with the primary goal of improving the FPs’ guideline adherence and reducing the proportion of second-line antibiotics, defined as quinolones, cephalosporins, co-trimoxazole and others. To improve guideline adherence and to change prescribing behaviour of FPs, we plan to: (1) collect resistance data on uropathogens in ambulatory care in Germany and (2) provide practices with this data, combined with current guideline recommendations in an appropriate way. The primary hypothesis is that a multimodal intervention can improve the guideline adherence of FPs when prescribing antibiotics for UTIs, specifically in reducing the prescription rate of second-line antibiotics. The secondary hypotheses are that the number of antibiotics prescribed for patients with a UTI will decrease, and the guideline information will be used and accepted by the practice teams.

## Methods/design

REDARES is a randomized controlled trial (RCT) based on aggregated patient data with family practices being the unit of randomization. The accompanying process evaluation provides information on applicability and acceptance of the intervention. Furthermore, the users' perspective will inform the study team about the potential need to adapt information material and strategy.

### Population

The primary target population are FPs, working in general practices in four federal states in Germany: Baden-Wuerttemberg, Bavaria, Berlin-Brandenburg and Thuringia. Private practices are excluded. FPs’ practices will be block-wise randomized into intervention or control group. The randomization will be stratified per region and will be conducted with the software SAS Version 9.4.

### Intervention

We developed a multimodal intervention consisting of (a) information on guideline recommendations and on regional resistance data and (b) feedback of prescribing behaviour for FPs aiming to translate knowledge from practice guidelines and research into practice and to facilitate implementation of guideline adherent treatment [21]. Practices in the intervention group will receive data on local pathogens and resistance rates as well as key guideline information on the management of uncomplicated UTIs for FPs and patients, in print or electronic form. Furthermore, practices will obtain feedback on their individual antibiotic prescribing performance compared to other regional and supra-regional practices and advisory services via telephone quarterly. Thus the intervention will include both, passive components of educational intervention and active methods, which are more likely to induce change [21]. The individual components of the intervention will be developed, incorporating the findings of current process evaluations. The intervention will be evaluated throughout the study period to determine contextual factors necessary to achieve the outcomes and to identify the resources required to implement the intervention [22, 23].

### Outcomes

The primary outcome is the prescription rate of second-line antibiotics for UTIs at practice level after 12 months, based on aggregated data. We defined the prescription rate of second-line antibiotics per practices as the proportion of second-line antibiotics of all prescribed antibiotics for UTI. Second-line antibiotics are defined as antibiotics not recommended for treating uncomplicated urinary tract infections according to the national guideline (other than: Trimethoprim, Pivmecillinam, Nitrofurantoin, Fosfomycin or Nitroxolin). The primary hypothesis is, that the intervention will reduce the prescription rate of second-line antibiotics prescribed by 10%, from 43% to 33% after 12 months. Further hypotheses are that the number of antibiotics prescribed for patients with a UTI will decrease, and the guideline information will be used and accepted by the practice teams.

The study will provide data on efficacy of a physician-directed, multimodal intervention in family medicine, and its practical application to the daily routine. The accompanying process evaluation will provide information on the applicability and acceptance of the intervention and will inform the study team about potential adaptation of materials and strategy from the users` perspective.

Due to the systematic development and flexibility of the intervention, we expect that this will be amenable to practices’ standard care, and independent of the respective forms of organisation within the practice, such as individual workflow, roles and tasks delegated to physician assistants, and the information systems used. Beyond that, the results may represent a basis for the development of similar strategies in the implementation of recommended guidelines in different medical contexts. The knowledge gained through the collection of prescribing data in different patient management systems (PMS) contributes highly to the ongoing development of individual feedback systems that require regular and reliable validations.

### Study procedures

The study consists of three phases, (1) the preparation phase (development), (2) the piloting phase and (3) the evaluation phase of the intervention (see also Fig. 1).

**Fig. 1 Fig1:**
[figure not shown]
Flowchart of the REDARES study

In the (1) preparation phase, the study team will develop components of the multimodal intervention (different guideline-orientated information for patients and FPs, information on regional resistance data, and regular feedback on physicians’ prescribing behaviour. (2) In order to adapt the study procedures to practice routines, the intervention was tested in a 6-month pilot phase before the start of the study in five non-participating practices. Adjustments based on individual feedback from the pilot practice teams were made as needed. The pilot phase did not affect the intervention itself, which will be the same in every practice. (3) The intervention and evaluation phase will be conducted in four regions in Germany as described above (see also population). After randomization, all intervention practices will be visited and provided with information on:The management of UTIs, including the current guideline recommendations, suggestions on how to use information for shared decision-making, information on resistance data (shown as a surveillance table), and several non-antimicrobial treatment approaches (delayed prescribing, painkillers, herbal remedies, etc.)How to deal with situations, such as differing patient preferences, guidance on treatment failure, and how to proceed with second-line antibiotics started by others

Intervention practices will receive individual feedback quarterly on their prescribing patterns, including benchmarking of all participating practices. They will have the opportunity to ask questions and receive oral feedback from a FP involved in the regional study team if they wish.

The effects observed in the intervention group will be compared to the control group (usual care). The control group will receive all intervention material after completion of the study. In the control practices, the physician assistants will then receive the training to obtain all data retrospectively. To reduce the interaction with the control practices and, thus, minimize potential bias, data sampling will be performed at the end of the study period in month 12 (see Fig. 1).

Process evaluation will start with FP interviews at the beginning of the intervention development process to assess what is locally feasible and acceptable. During intervention physician assistants and FPs from all intervention practices will complete a questionnaire about the feasibility of implementation in practice, generating important insight into this matter. Finally, after completion of the intervention phase, all practice teams will be asked to assess usability of the adapted intervention by a questionnaire in a group session with participating practices, results and final adaption of the intervention will be discussed.

### Data collection

Physician assistants will be trained to obtain treatment cases and data on prescribed antibiotics from the electronic patient record via a standardized training program to perform data sampling.

Data on UTI cases including number of UTI-related visits and antibiotics prescribed will be collected at practice level and transferred as aggregated data to the coordinating centre in Wuerzburg quarterly over a period of 12 months (see also Fig. 2). The final data extraction in the intervention practices will be performed 12 months after inclusion.

**Fig. 2 Fig2:**
[figure not shown]
Data flow in REDARES

In addition, data will be collected in the intervention practices retrospectively for the first quarter of the year prior to study start. In control practices, data of the same five quarters will be collected at the end of the last study quarter (see also Fig. 1).

The number of UTI-related treatments, ICD-classifications and the number of consultations will be obtained quarterly. Additional data including sociodemographic data (age, insurance status, urine culture, pregnancy, allergies, history of recurrent UTI, pyelonephritis and referrals to specialists or clinics due to UTI) will be collected at the end of the study separately, when the number of cases will be high enough to be in line with the European General Data Protection Regulation [24]. This is necessary because German family practices are usually small sized with around 1000–1500 patients per FP.

We will also collect sociodemographic data of FPs, including their gender, age, duration of practice, practice characteristics, such as the practice situation, whether rural or urban, whether the practice is staffed by a single FP or multiple FPs and the number of patient encounters per year. This data will be collected in anonymized paper–pencil form and transferred to the coordinating center.

### Data analysis

Data analysis will follow the intention-to-treat principle. All randomized practices will remain in the allocated arm for analysis. All analyses are based on aggregated data obtained at practice level. For the primary analysis, we will use an analysis of covariance (ANCOVA) with an adjustment for the baseline rate of prescribing. Descriptive analysis of the frequency and prescription rate of second-line antibiotics, and the frequency of all antibiotics prescribed, the number of cases, and the dose and class of prescribed antibiotic will be assessed. In the secondary analysis, we will also adjust for size and region of the practice using ANCOVA. Furthermore, we will seek to categorize practices into two groups: those with a high rate of prescribing second-line antibiotics, versus those with a low rate. A comparison will be made between these two groups based on their demographics and general patient characteristics, for instance the age distribution of the practice, using Chi^2^-Test, t-Test or Mann–Whitney U test. To investigate the effect of demographics and patient characteristics of the practice, a multivariable logistic regression of the probability of a low rate of prescribing second-line antibiotics will be assessed. All secondary analyses will be explorative, with a significance level of 5%. SAS, R or SPSS software will be used to analyze the data.

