### Sample size calculation

The primary endpoint will be the prescription rate of second-line antibiotics after 12 months. This will be measured at a practice level, and will be based on the aggregated data of each practice. A reduction in the rate of second-line antibiotic prescribing for UTIs is based on the following assumptions: in trials aiming to improve physicians’ guideline adherence, multimodal interventions such as training, focus groups and personal feedback, demonstrated a definite reduction in the prescribing rate of second-line antibiotics by more than 20% (absolute difference) [16, 17].

In comparison to former studies, REDARES aims to develop interventions without the need for expensive and time-consuming training or the provision of other educational media in participating practices. It is rather based on an information transfer and regular feedback, which, if proven effective, can be implemented in usual practice. Therefore, we would assume a conservative effect, in other words a 10% absolute reduction in the prescribing rate of second-line antibiotics. To adjust for differing baseline prescribing rates of second-line antibiotics, the sample-size calculation of the primary analysis was based on ANCOVA, with baseline prescribing rates as a covariate. Following Dicheva et al. 2015 [2] an assumption was made based on a quinolone prescribing rate of 43% of all antibiotics prescribed for women with a UTI. At the practice level, there is no data available for the standard deviation of prescribing rates. Therefore, we based our own experience on an assumed standard deviation of 20% and a moderate R^2^ of 0.25 of the covariate, equating to a correlation of 0.5 between the baseline and the prescribing rate after one year. To detect a 10% absolute difference in the prescribing rate after one year, between the control group (43%) and the intervention group (33%), a total sample size of 114 practices, 57 practices per group, are needed to achieve a power of 86% with a significance level of 5%. Assuming a dropout rate of 10% at the practice level, a sample size of 128 practices needs to be recruited.

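### Region stratifies the randomisation but is left out of the primary ANCOVA; if region predicts the 12-month rate beyond baseline, the primary test is conservative and its confidence interval too wide

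*Protocol article*

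**What the plan says.** Under Population, the article recruits practices in "four federal states in Germany: Baden-Wuerttemberg, Bavaria, Berlin-Brandenburg and Thuringia" and randomises them in blocks. On the strata it says: "The randomization will be stratified per region and will be conducted with the software SAS Version 9.4".

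Under Data analysis, the primary model is fixed as follows: "For the primary analysis, we will use an analysis of covariance (ANCOVA) with an adjustment for the baseline rate of prescribing". No other covariate is named. Region comes next, in a different role: "In the secondary analysis, we will also adjust for size and region of the practice using ANCOVA". The same section declares all secondary analyses exploratory.

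Under Sample size calculation, the trial is sized on the same model, an ANCOVA with the baseline prescribing rate as covariate.

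The article therefore names region and places it outside the confirmatory model. This is a stated choice and not a detail left to a statistical analysis plan that is not shown.

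**The concern.** Blocking within region nearly equalises the arms on region, so differences between regions largely drop out of the true error of the treatment comparison. A model without region does not know this and leaves the between-region variance in its residual. If region carries information on the 12-month rate that the baseline rate does not, the reported standard error is larger than the true one. The confidence interval is then wider than it need be, and the test rejects a true null less often than 5% of the time.

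What is at stake is the reported precision of the single confirmatory result, plus a little power. A regional effect is plausible on the article's own account: the Background says antibiotic choice should follow local resistance, and the intervention supplies regional resistance data. The documents do not say how large such an effect is once baseline is in the model.

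**Working it through.** **Inputs from Sample size calculation.** Difference 10 points (43% against 33%), SD 20 points, R² = 0.25 for baseline, 57 practices per group, significance level 5%, power 86%. Sidedness is not stated.

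**Reproducing the stated power.**
- Residual SD after baseline: 20 × √(1 − 0.25) = 17.32, so the residual variance is 300.
- Standard error of the difference: SE₀ = 17.32 × √(2/57) = 3.24.
- Two-sided power, normal approximation: Φ(10/3.24 − 1.96) = 86.9%. With the noncentral t on 111 degrees of freedom it is 86.3%.
- A one-sided test would give 92.5%, and no baseline adjustment would give 76.1%.

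The stated 86% is therefore the two-sided, baseline-only ANCOVA. The sample size is not in question.

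**Assumption.** Let f be the share of the variance left after baseline that region explains. The documents give no value for it. With residual variance 300, the between-region SD is √(300f): about 2.4 points at f = 2%, 3.9 at 5%, 5.5 at 10% and 7.7 at 20%. The total variance after baseline is held at 300 throughout.

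**Large-sample formulas.** With the arms balanced within region, the true standard error is SE₀√(1 − f), while the model without region reports SE₀. Hence:
- type I error without region = 2 × [1 − Φ(1.96/√(1 − f))]
- power without region = Φ[(10 − 1.96·SE₀)/(SE₀√(1 − f))]
- power with region = Φ[10/(SE₀√(1 − f)) − 1.96]

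At f = 10%, 1.96/√0.9 = 2.07, so the type I error is 3.9%. Power is 88.2% without region and 90.1% with it.

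**Simulation.** This uses the t reference distribution and strata that are not exactly balanced. Settings: 114 practices, strata of 29/29/28/28 and permuted blocks of 4 (both assumed), and baseline independent of region, so that f is purely the part beyond baseline. Each setting had 20,000 runs under the null and 10,000 under the 10-point difference.

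| f | Type I error without / with region | Power without / with region | Gain (points) | Mean reported SE without / with region |
|---|---|---|---|---|
| 0% | 4.9% / 5.0% | 86.3% / 86.2% | none | 3.25 / 3.25 |
| 2% | 4.8% / 4.9% | 86.6% / 87.0% | 0.4 | 3.25 / 3.22 |
| 5% | 4.7% / 5.1% | 87.0% / 88.3% | 1.3 | 3.25 / 3.17 |
| 10% | 4.1% / 5.1% | 86.8% / 89.1% | 2.3 | 3.25 / 3.09 |
| 20% | 2.9% / 5.0% | 88.1% / 92.4% | 4.3 | 3.26 / 2.91 |

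Simulation error is about √(0.05 × 0.95/20,000) = 0.15 points for the type I error and √(0.87 × 0.13/10,000) = 0.34 points for each power. The two models were fitted to the same simulated data. The formulas and the simulation agree on direction and order of size.

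**What is lost.** At f = 10% the empirical SD of the estimated difference is 3.09 under both models, so the estimate itself is no less precise without region. The model without region reports 3.25 instead of 3.09, a confidence interval about 5% too wide (3.25/3.09 = 1.05).

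**Cost of adding region when it explains nothing.** Noncentral-t power is 86.33% on 111 degrees of freedom and 86.32% on 108.

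**The case against.** The case for leaving the model alone has four parts.

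- **The consequence is conditional.** Stable regional prescribing habits would already show in each practice's baseline rate, which is in the model. The documents show no residual regional shift, and f could be close to zero. This stands. It is why the loss is given as a range that starts at nothing.
- **Planned performance is safe.** Power without region did not fall below the stated 86% in any setting, and type I error is never inflated, so the trial is protected against a false claim of benefit. This also stands and limits the weight of the point.
- **The plan is coherent.** The primary model matches the sample-size model, and a region-adjusted ANCOVA is prespecified. This is true, and there is no internal contradiction. But the region-adjusted result is only exploratory and brings in practice size as well, so it cannot serve as the confirmatory result.
- **An article condenses.** That would excuse silence about region. It does not apply here, because the article assigns region to the secondary analysis.

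A reader might infer that the primary test does run below 5% and does lose precision. The documents do not support that: both need region to predict the outcome beyond baseline, and no figure is given. A reader might also infer a biased estimate, an inflated type I error or an underpowered trial. The calculations show none of these.

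**Conclusion.** The point holds in conditional form. The randomisation uses region, and the confirmatory analysis does not. If region explains 2% to 5% of the variance left after baseline, the loss is small: a type I error of about 4.7% to 4.8% and 0.4 to 1.3 points of power. At 10% to 20% it becomes noticeable: about 4.1% to 2.9%, and 2.3 to 4.3 points. At 0% nothing is lost.

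These figures rest on the article's planning values, on the two-sided reading of its 5% level, and on assumed block size and stratum sizes. The omission itself is certain from the text; its practical size is not known. This is a worthwhile improvement because it costs almost nothing. It is not an error that threatens the primary result.

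**What to change.** In Data analysis, make the primary model an ANCOVA of the 12-month second-line prescribing rate on arm, baseline rate and region, with region as a four-level fixed effect. Keep practice size for the secondary model. The sample size need not change.

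The cost is one sentence and 3 degrees of freedom, with no measurable loss of power even if region explains nothing. No new data are needed, because each practice's region is known at randomisation. Making the change before the outcome data are analysed avoids any suspicion that the model was chosen on its result.

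### The exploratory determinants analysis splits a continuous prescribing rate into high and low and so gives up at least about a third of its information

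*Protocol article*

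**What the plan says.** Outcomes defines the prescription rate for each practice as "the proportion of second-line antibiotics of all prescribed antibiotics for UTI". This is a practice-level proportion, and the primary analysis in Data analysis treats it as continuous, using ANCOVA with the baseline rate as covariate.

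The same section then turns to practice characteristics: "we will seek to categorize practices into two groups: those with a high rate of prescribing second-line antibiotics, versus those with a low rate". The two groups are to be compared on demographics and general patient characteristics by chi-squared, t or Mann–Whitney tests. A model follows, meant to show how the make-up of a practice and its patients relates to prescribing: "a multivariable logistic regression of the probability of a low rate of prescribing second-line antibiotics will be assessed". No clinical or guideline threshold is offered as a reason for the split.

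On status the section says: "All secondary analyses will be explorative, with a significance level of 5" per cent.

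The candidate characteristics appear in Data collection. The patient items (among them urine culture and referrals) are gathered at the end of the study. The physician and practice items include age, gender, location and staffing.

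**The concern.** The plan already models the full rate for its main comparison, then sets that information aside for this one question. After a split, a practice just below the cut counts the same as one far below it, and two practices on either side of the cut count as opposites. Real associations between practice characteristics and prescribing become harder to detect, and estimates become less precise.

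With 114 practices there is little to spare. Even at an even split the smaller outcome group holds only 57. At stake is what the trial can say about which kinds of practice prescribe fewer second-line drugs. The estimate of the intervention effect is not at stake.

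**Working it through.** **Inputs from the protocol (Sample size calculation).** 57 practices per group, 114 in total; 43% against 33%; SD 20 points; R² 0.25 for the baseline covariate; 5% level; power 86%; 10% dropout; 128 recruited. The protocol gives no figure for the determinants analysis.

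**The plan's own figure.** 
- Residual SD = 20 × √(1 − 0.25) = 17.32. 
- Standard error = 17.32 × √(2/57) = 3.244, and 10/3.244 = 3.08. 
- Two-sided 5% power: Φ(3.08 − 1.96) = 0.869 by the normal approximation, 0.863 by the noncentral t with 111 degrees of freedom. 
- 57/0.9 = 63.3, rounded up to 64 per group, gives 128. 

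The stated 86% and 128 reproduce, so 114 analysed practices is a sound basis for what follows.

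**Information kept after a split.** For a normal outcome cut so that a share p is low, the relative efficiency for small effects is φ(c)²/[p(1 − p)], where c is the normal quantile of p.

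| Share in smaller group | Kept | Lost | 114 practices act like |
|---|---|---|---|
| 0.50 | 0.637 (= 2/π) | 36% | 0.637 × 114 = 72.6 |
| 0.33 | 0.593 | 41% | 67.6 |
| 0.25 | 0.539 | 46% | 61.4 |
| 0.20 | 0.490 | 51% | 55.9 |

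The median split is the best case.

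**Effect on power.** Take a characteristic with correlation 0.26 to the rate. This value is an assumption, chosen because it gives about 80% power in the linear model. 
- Continuous: atanh(0.26) × √111 = 0.2661 × 10.54 = 2.80, and Φ(2.80 − 1.96) = 0.80. 
- Median split: 2.80 × √0.637 = 2.24, and Φ(2.24 − 1.96) = 0.61. 

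Simulations at n = 114 with 2,000 runs per setting agree: 78–81% for linear regression and 57–60% for logistic regression on the split.

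**Does arm distort the associations?** Suppose the 12-month rate is split at 38% (the midpoint of 33 and 43) with both arms together. Then Φ(−5/20) = 40.1% of control and Φ(5/20) = 59.9% of intervention practices are low, about 23 against 34 of 57, an odds ratio of (0.599/0.401)² = 2.23. What follows depends on the kind of characteristic:
- *Independent of arm (fixed before randomisation).* With no true association and a 10-point intervention effect, leaving arm out gave 3.8% false positives in the logistic model and 4.6% in the linear one. With a true association, the logistic coefficient was −0.434 without arm and −0.449 with it.
- *Shifted by the intervention.* For a characteristic with no association of its own, moved by an assumed 0.25, 0.5 or 0.8 SD in the intervention arm, logistic false positives without an arm term were about 6%, 8% and 12%. With arm in the model they were 4–5%.

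**The case against.** The strongest defence is that little depends on this analysis. It is labelled exploratory, determinants of low prescribing are not among the stated hypotheses, and the primary ANCOVA keeps the rate continuous. That stands, and it sets the severity. It does not make the split a good choice, because the split is a stated method and not a detail left for an analysis plan.

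A second defence is that the figures rest on a normal rate, a median cut and a chosen correlation. That is also correct. The normality and the 0.26 are assumptions, while the median cut is the one most favourable to the plan.

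A reader might go further in three ways that the protocol does not support.
- *That the analysis mixes practice characteristics with the intervention effect.* Data analysis states neither that the arms are pooled nor whether the baseline or the 12-month rate is split. At baseline there is no intervention effect to mix in. At 12 months, randomisation makes characteristics fixed beforehand independent of arm in expectation, and the simulation shows no excess of false positives. Only end-of-study patient variables that the intervention could change, such as urine culture or referrals, carry some risk.
- *That the model has about four events per covariate.* This figure (57/14) assumes that all 8 patient and 6 physician or practice items enter one model. The protocol lists them as collected, not as jointly modelled.
- *That the physician and practice form cannot be linked to a practice's rate.* Data collection does say "This data will be collected in anonymized paper" form. The inference rests on one word, and coding procedures are detail that an article commonly omits.

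**Conclusion.** The point holds as a minor one about efficiency. Splitting the rate and fitting a logistic model loses about 36% of the information at best, and 41–46% at a one-third or one-quarter cut, if the rate is roughly normal. For an assumed correlation of 0.26, this is a fall in power from about 80% to about 60% with 114 practices. The loss affects only the exploratory determinants analysis; the primary analysis, its sample size and its conclusion are unaffected. The documents do not support a general claim that the intervention effect contaminates the associations.

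**What to change.** Make the main determinants model a regression of the continuous practice rate on the practice, physician and patient characteristics. It can be linear, or a grouped binomial model of second-line out of all UTI antibiotics with an allowance for overdispersion. Keep the high/low table as description only.

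State which rate is modelled: the baseline rate, or the 12-month rate with arm as a covariate. At 12 months the arm term guards against spurious associations for end-of-study patient variables. Adjusting the 12-month rate for baseline is not part of this change, because it would turn the question from which practices prescribe low into which practices changed.

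The cost is a change of wording in the analysis plan, with no extra practices or data. The one drawback is that the linear model reports differences in rate and not odds of being a low prescriber, which is arguably easier to read beside the primary result.
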